1. stimulating a bifidogenic flora
2. preventing adhesion of pathogens to epithelial tissues
3. stimulation of Th1 cytokine response (e.g. TNF-, IFN-gamma) and decreasing the Th2 cytokine release (e.g. IL-10, IL-4, IL-5)
4. improvement of the response to immunizations

As a result of these effects, it is thought that infants receiving a combination of GOS/FOS with AOS will have:

1. less infections
2. less feeding intolerance
3. less atopy later in life

As infections are still a major cause of morbidity and mortality, reducing the incidence of serious infections is very important. As controversy exist on the definitions for serious infections in neonates, we redefined in a previous study the CDC criteria for serious infections in neonates1 and found these criteria applicable in a study in preterm infants.14

In the current study, we want to determine the effect of enteral supplementation of acidic and neutral oligosaccharides on the incidence of serious infections, using the previously described criteria for serious infections in preterm infants at high risk for serious infections, with a gestational age < 32 weeks and/or a birthweight < 1500g.

In conclusion, this double-blind randomised controlled trial has the following aims:

1. To determine the effect of acidic and neutral oligosaccharides supplemented enteral nutrition on infectious morbidity, intestinal microflora, feeding tolerance, and short-term outcome in VLBW infants.
2. To elucidate the role of acidic oligosaccharides in modulation of the immune response and postnatal adaptation of the gut.
3. To determine the long term effects of acidic and neutral oligosaccharides supplemented enteral nutrition in the neonatal period on the development of allergic and infectious disease in the first years of life (by questionnaire) and neurodevelopmental outcome, neuromotor development at the corrected age of 1 and 2 years and mental/motor development (BSIDII) at the corrected age of 2 years (as part of the regular follow-up of NICU infants).

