## Study population

Infants with a gestational age <32 weeks and/or birth weight <1500 g admitted to the level III neonatal intensive care unit (NICU) of the VU University Medical Center, Amsterdam, are eligible for participation in the study. Written informed consent is obtained from all parents.

Exclusion criteria are: major congenital or chromosomal anomalies, death <48 h after birth, transfer to another hospital <48 h after birth and admission from an extraregional hospital.

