Faecal samples are stored at -20oC until analysis by fluorescent in situ hybridisation (FISH) using specific 16S rDNA-targeted probes as described by Harmsen et al.3 gastrointestinal transit time (GGT) will be measured by adding 20 mg carmine red to 1 feeding. GGT is defined as the time from feeding the marker to its appearance in the diaper.19 Stool pH will be measured using a Handy lab pH meter.20

*Immune response*

The effect of acidic and neutral oligosaccharide supplemented enteral nutrition on the immune response is investigated by determining the development of the immune response to Diphteria - Tetanus – acellular Pertussis - inactivated Polio-Haemophilus influenza type B - Pneumococcus (DTaP-IPV-HiB-Pneu) immunizations (first 3 doses), and if indicated Hepatitis B vaccin, and the development of the memory function of the immune response to these immunizations by measuring the response to the 4th booster dose. In addition, the plasma cytokine concentrations (Il-2, Il-4, IL-5, Il-8, IL-10, TGF α, IFN γ), faecal calprotectin and IL-8 concentrations will be measured.

*Follow-up*

To investigate neurodevelopmental outcome, neuromotor development at the corrected age of 1 and 2 years21 and mental/motor development (BSIDII) at the corrected age of 2 years are assessed.22

To determine the incidence of allergic and infectious disease in the first year of life, faecal samples (FISH, calprotectin and IL-8) and IgE/IgG4 levels will be measured at 5 and 12 months and questionnaires will be sent to the parents prior to the follow-up visit at the corrected age of one year.

To determine the frequency of side-effects of immunizations, questionnaires will be given to the parents at the time of immunizations.23

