**Statistical analysis**

To determine whether randomisation is successful, prognostic similarity (perinatal and nutritional characteristics) between treatment groups is assessed. The Students’ t-test, Mann-Whitney U test, and chi-square test or Fisher’s exact test are used to compare continuous normally distributed, nonparametric continuous and dichotomous data respectively.

Logistic regression is performed to examine whether acidic and neutral oligosaccharide supplemented enteral nutrition decreases the incidence of serious infections. In an additional analysis, adjustments are made for possible confounding factors as administration of antenatal corticosteroids, birth weight <p10, administration of breast milk and other prognostic factors that may be different between treatment groups.

Analyses of secondary outcomes (only crude) is performed by Mann-Whitney U test, chi-square test or Fisher’s exact test and log rank test for nonparametric continuous, dichotomous data and time-dependent data respectively.

Generalised estimated equations for longitudinal analysis24 are used to analyse changes over time in intestinal permeability, faecal microflora, faecal IL-8 and calprotectin, and plasma Th1/Th2 cytokine concentrations.

Distribution of optimal and non-optimal neuromotor development and normal and abnormal mental/motor development in oligosaccharides and control groups is examined by logistic regression with adjustments for possible confounding factors as gestational age and birth weight.

All statistical analyses are performed on an intention to treat basis. In addition, alternative per protocol analyses are performed, excluding all patients who are not treated according to protocol, defined as more than 3 consecutive days or a total of 5 days on minimal enteral feeding or without supplementation. For all statistic analyses a p value <0.05 is considered significant (two-tailed). SPSS 12.0 (SPSS Inc., Chicago, IL, USA) and STAT 7.0 (StatCorp LP, College Station, TX, USA) are used for data analysis.

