Appendix 1: Case record form

Appendix 2: Questionnaire side effects vaccinations

**Tables**

### Table 1 Clinical outcome measures

|  |  | Remarks |
| --- | --- | --- |
| Infectious morbidity |  |  |
| Serious infections |  | Primary outcome |
| Number of infectious episodes |  |  |
| Cultured micro-organisms |  |  |
| Feeding tolerance |  |  |
| Enteral feeding >120 mL/kg/day |  |  |
| Age at finishing parenteral nutrition |  |  |
| Necrotising enterocolitis |  | Bell et al.[15] |
| Weight *z* scores at birth, day 30 and at discharge |  | Usher et al. [25] |
| Patent ductus arteriosus |  |  |
| Ventilatory support |  |  |
| Use of oxygen at postmenstrual age of 36 weeks |  | Jobe et al. [26] |
| Intraventricular hemorrhage |  | Papile et al. [27] |
| Retinopathy of prematurity |  | Committee for ROP [28] |
| Death |  |  |
| Age at discharge from NICU and at discharge home |  |  |
| ROP= retinopathy of prematurity; NICU = neonatal intensive care unit. | | |

Table 2: Study schedule

| **Postnatal age** |  | **< 48h** | **day 4** | **day 7** | **day 14** | **day 30** | **5 mo** | **1 yr** |
| --- | --- | --- | --- | --- | --- | --- | --- | --- |
| **Faeces** |  |  |  |  |  |  |  |  |
| Faecal  Calprotectin  /IL-8 |  | x | - | x | x | x | x | x |
| Intestinal  microflora  FISH / pH |  | x | - | x | x | x | x | x |
| Gastrointesti-  nal transport  time |  | - | - | - | x | - | - | - |
| **Urine** |  |  |  |  |  |  |  |  |
| Intestinal  permeability |  | x | x | x | - | - | - | - |
| **Blood** |  |  |  |  |  |  |  |  |
| Cytokine profile | 0,5ml | x | - | x | x | - | - | - |
| IgE/IgG4 | 0,6ml | - | - | - | - | - | x | x |
| Immune  response | 2,0ml | - | - | - | - | - | x | x |

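### Development at 1 and 2 years and oxygen use at 36 weeks can be scored only in infants still alive, so these comparisons condition on survival and are not fully intention-to-treat

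*Protocol*

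**What the plan says.** For follow-up, the Statistical analysis section of the protocol fixes a two-category outcome and a model: "Distribution of optimal and non-optimal neuromotor development and normal and abnormal mental/motor development in oligosaccharides and control groups is examined by logistic regression". The model is to be adjusted for baseline factors, of which birth weight and gestational age are given as examples. Under Study outcome measures (Follow-up), neuromotor development is assessed at corrected ages 1 and 2 years, and the BSIDII at 2 years.

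Table 1 lists "Use of oxygen at postmenstrual age of 36 weeks" among the clinical outcomes. Death has its own row, with no time horizon. For secondary outcomes the Statistical analysis section states: "Analyses of secondary outcomes (only crude) is performed by Mann-Whitney U test, chi-square test". The oxygen comparison is therefore unadjusted.

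The same section then says: "All statistical analyses are performed on an intention to treat basis". Under Study population, the exclusion for early death reaches only "death <48 h after birth", so infants who die later stay in their allocated group. The protocol defines no outcome that combines death with development or with oxygen use, and gives no other handling of infants who die before assessment.

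**The concern.** The binary models have no category for an infant who died. Once any infant dies after 48 hours, the stated model and the intention-to-treat statement cannot both hold in full for these outcomes. What can be compared is survivors in one arm with survivors in the other, and randomisation does not protect that comparison if survival depends on treatment.

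A treatment effect on survival is plausible on the protocol's own reasoning. The Background says "As infections are still a major cause of morbidity and mortality", and the trial is sized to detect a fall in serious infection from 76% to 50%. If some infants survive because of the supplement and are at higher risk of impairment or prolonged oxygen need, they raise the event rate among supplement survivors. Their control counterparts died and do not appear at all. Neurodevelopment is one of the trial's stated aims, so a distorted comparison there would matter.

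Adjustment for gestational age and birth weight removes only the part of this selection that those two variables explain. The crude oxygen comparison removes none of it.

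**Working it through.** **The plan's own figure.** The only relevant stated number is the sample size. By the protocol's formula, 2 × 7.85 × 0.63 × 0.37 / 0.26² = 54.1, so 54 per arm, as stated. Power at 54 per arm for 76% v 50% is 80.8%. This figure is not in dispute and serves only as the denominator below.

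**Inputs that must be assumed.** The protocol gives no rate for death, abnormal development or oxygen use. Let
- m = control mortality (10, 15 or 20%);
- s = absolute mortality reduction (2, 5 or 8 points), so supplement mortality is m − s;
- b = abnormal rate in infants who would survive in either arm (25%), with no supplement effect on them;
- q = abnormal rate in infants saved by the supplement (25, 50, 80 or 100%).

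**Formulas.**
- Survivors only, control: b. Supplement: [(1 − m)b + sq] / (1 − m + s).
- Death or abnormal, control: m + (1 − m)b. Supplement: (m − s) + (1 − m)b + sq.
- The difference in death-or-abnormal is therefore −s(1 − q).

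**Central case** (m = 15%, s = 5 points, q = 80%).
- Survivors only: 25.0% v (0.85 × 0.25 + 0.05 × 0.80)/0.90 = 0.2525/0.90 = 28.1%, odds ratio 1.17.
- Death or abnormal: 0.15 + 0.2125 = 36.25% v 0.10 + 0.2525 = 35.25%.

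The two comparisons point in opposite directions.

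**Range over the whole grid.**

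| Case | Survivors-only difference | Odds ratio | Death-or-abnormal difference |
| --- | --- | --- | --- |
| q = 25%, s = 8 points | 0 | 1.00 | −6.0 points |
| m = 15%, s = 5 points, q = 80% | +3.1 points | 1.17 | −1.0 point |
| m = 20%, s = 8 points, q = 100% | +6.8 points | 1.40 | 0 |

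In the last row the supplement arm has 54 × 0.88 = 47.5 survivors, and 6.8% of 47.5 is about 3 infants.

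**Offsetting benefit.** In the central case, suppose the supplement also lowers the abnormal rate among the other survivors by 4 points. The survivors-only result is then (0.85 × 0.21 + 0.04)/0.90 = 24.3% v 25.0%, and the apparent harm is gone.

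**Oxygen at 36 weeks** (assumed 30% in infants who survive in either arm, mortality 15% v 10%, all saved infants on oxygen).
- Survivors only: 30.0% v (0.255 + 0.05)/0.90 = 33.9%.
- Death or oxygen: 0.15 + 0.255 = 40.5% v 0.10 + 0.305 = 40.5%.
- If the dead were kept in the denominator as not on oxygen: 25.5% v 30.5%, a larger distortion.

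**Illustration in counts** (assumed: 54 per arm; control 8 deaths, 10 abnormal survivors, 36 normal survivors). If the supplement prevents k deaths and every saved infant is abnormal, the 36 normal survivors are unchanged and the survivors-only odds ratio is (10 + k)/10.
- k = 2: 12/48 (25%) v 10/46 (22%), odds ratio 1.2.
- k = 4: 14/50 (28%) v 10/46, odds ratio 1.4.
- k = 6: 16/52 (31%) v 10/46, odds ratio 1.6.

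Death or abnormal is (8 − k) + (10 + k) = 18 of 54 in both arms throughout. This example takes q at its extreme, and k = 6 means 6/54 = 11 points saved, which is outside the grid above.

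**The case against.** The Statistical analysis section never says that deaths are excluded. Handling of deaths and missing scores in secondary outcomes is often left to a SAP, which is not shown here, and the intention-to-treat sentence may mean only that infants are analysed as allocated, in contrast to the per-protocol set that follows it. This limits the point but does not remove it. The protocol itself chose the categories, the model and the analysis basis, and those categories cannot hold an infant who died.

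A reader might infer that a supplement which saves the sickest infants would necessarily look harmful. The documents do not support that. It needs a mortality difference, worse outcomes in the saved infants and no offsetting benefit in the others, and no mortality rate is given. Nor is a survival effect part of the stated hypothesis: the Background lists fewer infections, less feeding intolerance and less atopy as the expected effects, and mentions mortality only to explain why infection matters.

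Chance is also large beside the bias. For 14/50 v 10/46 the standard error of the log odds ratio is √(1/14 + 1/36 + 1/10 + 1/36) = 0.476, so the 95% interval around 1.4 runs from about 0.55 to 3.6.

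Two further objections shape the remedy. A composite can hide a survival gain: in the count example up to 6 deaths are prevented and the composite shows 18/54 in both arms. Death is already a Table 1 outcome, so a mortality difference would be visible anyway. These are reasons to place the composite beside the survivors-only result and the deaths by arm, not in place of them. It also cannot be assumed that every death is already captured, because Table 1 gives death no time horizon.

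**Conclusion.** The point holds as a limited one. Neuromotor development at 1 and 2 years, BSIDII at 2 years and oxygen use at 36 weeks are defined only for infants alive at assessment. As written, their comparison conditions on survival after randomisation and is not fully intention-to-treat. The result could be biased toward apparent harm. Under the assumed rates the shift is 0 to about 7 percentage points (odds ratio 1.00 to 1.40), and it is zero when saved infants fare no worse than the others. That range rests entirely on assumed mortality and outcome rates. The affected outcomes are secondary and follow-up measures.

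**What to change.** In the Statistical analysis section, add three outcomes, counting deaths up to each assessment and analysed by allocated arm:
- death or non-optimal neuromotor development, at 1 and at 2 years corrected age;
- death or abnormal mental/motor development at 2 years corrected age;
- death or oxygen use at 36 weeks postmenstrual age.

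Report each beside the survivors-only result, labelled as conditional on survival, and beside the number of deaths in each arm. In Table 1, give death a time horizon that reaches each assessment. Survivors lost to follow-up still have no score, so a missing-data rule is needed for them as well.

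The cost is mainly wording, plus confirming vital status to 2 years corrected age where regular follow-up does not supply it. The downside is that a composite mixes death with impairment and can mask opposite effects, so its components must always be shown.

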## Summary

## Background

Prevention of serious infections in very low birth weight (VLBW) infants is a challenge, since prematurity and low birth weight often requires many interventions and high utility of devices. Furthermore, administration of enteral nutrition is limited by immaturity of the gastrointestinal tract. The acid and neutral oligosaccharides play an important role in the development of the intestinal bacterial colonisation and functional integrity of the gut. In preterm infants, the intestinal bacterial colonisation is delayed compared with term infants with possible negative effects on susceptibility to serious infections. An abnormal intestinal bacterial colonisation may also have negative effects on functional integrity of the gut and may lead to impaired function of the immune system. This double-blind randomised controlled trial is designed to investigate the effect of acidic and neutral oligosaccharides supplemented enteral nutrition on infectious morbidity, feeding tolerance and short-term outcome in VLBW infants. Furthermore, an attempt is made to elucidate the role of acidic oligosaccharide supplemented enteral nutrition in postnatal adaptation of the gut and modulation of the immune response.

### Methods

VLBW infants (gestational age <32 weeks and/or birth weight <1500 g) are randomly allocated to receive 1,5g/kg enteral acidic and neutral oligosaccharides (20%/80% mixture) supplementation or placebo (maltodextrin) supplementation between day 3 and 30 of life. Primary outcome is infectious morbidity (defined as the incidence of serious infections). Furthermore, feeding tolerance (defined as a feeding volume ≥120 mL/kg/day), short-term outcome and follow-up are evaluated. The effect of enteral acidic and neutral oligosaccharides supplementation on postnatal adaptation of the gut is investigated by measuring intestinal permeability and determining faecal microflora. The role of acidic and neutral oligosaccharides in modulation of the immune response is investigated by determining immune response to DtaP-IPV-HiB immunizations, plasma cytokine concentrations, faecal calprotectin and IL-8.

Appendix 1: Case record form

Appendix 2: Questionnaire side effects vaccinations

**Tables**

### Table 1 Clinical outcome measures

|  |  | Remarks |
| --- | --- | --- |
| Infectious morbidity |  |  |
| Serious infections |  | Primary outcome |
| Number of infectious episodes |  |  |
| Cultured micro-organisms |  |  |
| Feeding tolerance |  |  |
| Enteral feeding >120 mL/kg/day |  |  |
| Age at finishing parenteral nutrition |  |  |
| Necrotising enterocolitis |  | Bell et al.[15] |
| Weight *z* scores at birth, day 30 and at discharge |  | Usher et al. [25] |
| Patent ductus arteriosus |  |  |
| Ventilatory support |  |  |
| Use of oxygen at postmenstrual age of 36 weeks |  | Jobe et al. [26] |
| Intraventricular hemorrhage |  | Papile et al. [27] |
| Retinopathy of prematurity |  | Committee for ROP [28] |
| Death |  |  |
| Age at discharge from NICU and at discharge home |  |  |
| ROP= retinopathy of prematurity; NICU = neonatal intensive care unit. | | |

Table 2: Study schedule

| **Postnatal age** |  | **< 48h** | **day 4** | **day 7** | **day 14** | **day 30** | **5 mo** | **1 yr** |
| --- | --- | --- | --- | --- | --- | --- | --- | --- |
| **Faeces** |  |  |  |  |  |  |  |  |
| Faecal  Calprotectin  /IL-8 |  | x | - | x | x | x | x | x |
| Intestinal  microflora  FISH / pH |  | x | - | x | x | x | x | x |
| Gastrointesti-  nal transport  time |  | - | - | - | x | - | - | - |
| **Urine** |  |  |  |  |  |  |  |  |
| Intestinal  permeability |  | x | x | x | - | - | - | - |
| **Blood** |  |  |  |  |  |  |  |  |
| Cytokine profile | 0,5ml | x | - | x | x | - | - | - |
| IgE/IgG4 | 0,6ml | - | - | - | - | - | x | x |
| Immune  response | 2,0ml | - | - | - | - | - | x | x |
